### General analytic principles

The analyses of the outcomes will be based on the intention-to-treat principle, meaning that all participants will be analyzed in the group they were randomized to. For each group, we will report the proportion of participants who are randomized, the ones who receive a rhythm control strategy, and those who do not achieve the allocated heart rate target and the reason why.

We define our threshold for statistical significance as a *p*-value of 0.05, and assessments of clinical significance will be based on the anticipated intervention effects defined in the sample size and power estimations. Thresholds for both statistical and clinical significance will be assessed according to the 5-step procedure proposed by Jakobsen and colleagues [18].

We will adjust all regression analyses for the stratification variables we used for the randomization process and continuous outcomes will additionally be adjusted for the baseline value of the variable [19–21].

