#### Lenient rate control

For lenient rate control, the treatment provider will target the highest tolerable resting heart rate < 110 bpm assessed on a 12-lead resting ECG measured over 1 min after 5 min of rest. If the heart rate is below 90 beats per minute, the responsible physician is encouraged to reduce rate-controlling drugs.

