#### Strict rate control

For strict rate control, the treatment provider will target a mean resting heart rate of 70 bpm, but < 80 bpm is acceptable. The heart will be assessed on a 12-lead resting ECG measured over 1 min after 5 min of rest.

A more detailed description of the interventions can be found in the protocol, which previously has been published [3].

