#### Subgroup analysis

The subgroup analyses will be performed for primary and secondary outcomes and all subgroup analyses will be regarded as hypothesis-generating only. These analyses will be tested for interactions using test of interaction (interaction between the treatment variable and the subgroup indicator) in STATA 17 [8].

We will compare the following subgroups between the intervention arms:Patients with heart failure (including subtypes) compared to patients without heart failure [9]◦ Heart failure with reduced ejection fraction LVEF ≤ 40% or mildly reduced ejection fraction LVEF 41–49% (HFrEF and HFmrEF)◦ Heart failure with preserved ejection fraction LVEF ≥ 50% (HFpEF)Patients compared by their New York Heart Association (NYHA) class◦ NYHA class: I◦ NYHA class: II◦ NYHA class: III and IVPatients who are men compared to patients who are womenPatients compared based on their different durations of atrial fibrillation at randomization. The starting point of the duration of atrial fibrillation will be defined by when the patient was clinically diagnosed with persistent atrial fibrillation◦ Less than 1 year◦ 1 to 2 years◦ More than 2 yearsPatients who are 75 years of age or older compared to patients below 75 years of agePatients according to the modified European Heart Rhythm Association (mEHRA) symptoms score [10]◦ mEHRA score: 1, 2a, and 2b◦ mEHRA score: 3 and 4Patients having persistent atrial fibrillation compared to patients having permanent atrial fibrillation. Persistent atrial fibrillation defined as atrial fibrillation for more than 7 days and permanent atrial fibrillation defined as where only rate control is considered going forwardPatients achieving the target heart rate compared to patients not achieving the target heart rate

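### The subgroup split by whether the target heart rate was reached is formed after randomisation, with a different limit in each arm, so its between-arm comparisons can be biased in a direction that cannot be known in advance

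*SAP article*

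**What the plan says.** In the SAP article, General analytic principles bases the outcome analyses on randomised group: "based on the intention-to-treat principle, meaning that all participants will be analyzed in the group they were randomized to". The same section uses target achievement descriptively, reporting for each group who did not reach the allocated rate and why.

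The Subgroup analysis section opens its list with "We will compare the following subgroups between the intervention arms" and specifies a test of interaction between treatment and subgroup. It sets the scope and status as follows: "The subgroup analyses will be performed for primary and secondary outcomes and all subgroup analyses will be regarded as hypothesis-generating only". The last of the eight factors is whether or not the target heart rate was reached. The other seven (heart failure, NYHA class, sex, duration of atrial fibrillation, age, mEHRA score, type of atrial fibrillation) describe the patient at entry.

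The target differs by arm. Under Lenient rate control it is "the highest tolerable resting heart rate < 110 bpm", with the addition "If the heart rate is below 90 beats per minute, the responsible physician is encouraged to reduce rate-controlling drugs". Under Strict rate control it is "a mean resting heart rate of 70 bpm, but < 80 bpm is acceptable". The exclusion criteria remove patients whose resting rate before randomisation is below 80 bpm.

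**The concern.** A subgroup analysis keeps the protection of randomisation only if the factor is fixed before treatment starts. Target achievement is not. It depends on the assigned strategy and on how readily the patient's rate can be controlled, and it is judged against a different limit in each arm.

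Because entry requires at least 80 bpm, nobody in the strict arm meets the target at baseline, whereas a lenient participant entering at 80 to 109 bpm is already below the lenient limit. Strict achievers have therefore had to respond to treatment, and lenient achievers need not have. Comparing the arms within 'achieved', or within 'not achieved', compares different kinds of patient. The planned covariates (site, type of atrial fibrillation, LVEF category and, for continuous outcomes, the baseline score) do not measure how easily a rate is brought down, so they need not restore comparability. For hospital-free days and serious adverse events there is a further route: an early event can itself prevent a participant from reaching the target.

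At stake is the meaning of this one exploratory result. A difference inside either subgroup could arise with no treatment effect in anyone, on the question closest to the trial's purpose.

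**Working it through.** **The plan's own figure.** Sample size gives a difference of 3, SD 10, power 80% and type I error 5% (taken as two-sided). Per arm: 2 × (1.960 + 0.842)² × 10² / 3² = 174.4, so 175, or 350 in total. The stated 350 is reproduced and is not in question.

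**Inputs for the illustration.** From the plan: SD 10, 175 per arm, important difference 3. Assumed, because the plan gives none of them: the proportions reaching target (67% strict, 95% lenient), the correlation r between ease of rate control and the 12-month physical component score, and no true effect in anyone.

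**Formula.** Suppose a participant reaches target when a standard normal 'ease of control' exceeds an arm-specific cut-off. With proportion p reaching target and z = Φ⁻¹(p), the mean shift in score is 10·r·φ(z)/p for achievers and −10·r·φ(z)/(1 − p) for non-achievers.

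**Numbers at r = 0.3.**
- Strict, p = 0.67: z = 0.440, φ(z) = 0.362. Achievers: 10 × 0.3 × 0.362/0.67 = +1.62. Non-achievers: −10 × 0.3 × 0.362/0.33 = −3.29.
- Lenient, p = 0.95: z = 1.645, φ(z) = 0.103. Achievers: +0.33. Non-achievers: −6.19.
- Strict minus lenient, from unrounded values: **+1.30** among achievers and **+2.90** among non-achievers.
- Whole arms: 0.67 × 1.62 − 0.33 × 3.29 = 0, and likewise 0 for lenient. The randomised comparison remains unbiased.

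**Range (unadjusted, strict minus lenient).**

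| Strict / lenient reaching target | r | Achievers | Non-achievers |
|---|---|---|---|
| 67% / 95% | 0.1 | +0.43 | +0.97 |
| 67% / 95% | 0.2 | +0.86 | +1.93 |
| 67% / 95% | 0.3 | +1.30 | +2.90 |
| 60% / 90% | 0.3 | +1.35 | +2.37 |
| 67% / 85% | 0.3 | +0.80 | +1.37 |
| 80% / 80% | any | 0 | 0 |
| any | 0 | 0 | 0 |
| 67% / 95% | −0.3 | −1.30 | −2.90 |

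**Baseline adjustment.** If the baseline and 12-month scores correlate 0.6 and the baseline score carries part of the selection, the r = 0.3 figures fall to about 0.9 and 1.9. In simulation the comparison among achievers is then falsely significant in about 14% of trials. That rate falls to about 9% if 85% of the lenient arm reach target, or if the baseline score correlates with ease of control as strongly as the 12-month score does. At r = 0.1 it is about 6%.

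**Precision.** Expected non-achievers are 175 × 0.33 = 58 strict and 175 × 0.05 = 9 lenient. The unadjusted standard error of that contrast is 10 × √(1/57.75 + 1/8.75) = 3.6 points. Among achievers it is 10 × √(1/117.25 + 1/166.25) = 1.2.

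**The interaction test.** The two subgroup differences are 1.30 − 2.90 = −1.60 apart, with standard error √(3.6² + 1.2²) = 3.8, a ratio of about 0.42. Two-sided rejection at 5% is then P(Z > 1.54) + P(Z < −2.38) ≈ 0.07. Simulation gives about 6 to 8%.

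**Other patterns.** If selection acts in the strict arm alone, the adjusted differences are +1.0 among achievers and −2.2 among non-achievers. The interaction test is then falsely significant in 18% (95% lenient achievement) to 32% (85%) of trials. If lenient achievement were read as a band, so that low rates counted as not achieved, one scenario (70% / 95%, r = 0.3) gave +2.63 and −5.56. Neither size nor sign is stable across plausible readings.

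**The case against.** The strongest reply has four parts.

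First, a reader might infer that the subgroup list contradicts the intention-to-treat statement. It does not. That statement is about the arm in which a participant is analysed, and the subgroup analysis keeps everyone in the randomised arm. What is lost is comparability within the subgroups.

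Second, a reader might infer that the analysis will favour strict control in both subgroups. The documents do not support that. They give neither achievement proportions nor a correlation. A negative correlation makes strict control look worse in both subgroups, a zero correlation gives no bias, and other selection patterns give opposite signs. The figure of 2.9 should not be set beside the important difference of 3 without its qualifications: it is unadjusted and rests on about 9 lenient participants.

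Third, the test the plan names is the interaction test, and it is barely affected in the main illustration. The larger rates of 18 to 32% belong to a different model and cannot be combined with the two-sided advantage for strict control. This stands as a limit on size. It does not rescue the within-subgroup estimates, which the section also sets out to compare between arms.

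Fourth, the section calls all subgroup results hypothesis-generating, and the Outcomes section rests the primary conclusions on the primary outcome. This limits the weight of the result. It does not cure a structural bias, which a larger sample would only estimate more precisely.

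**Conclusion.** The structural point holds. Of the eight subgroup factors, this one is a consequence of treatment and is defined differently by arm, so its between-arm comparisons are not protected by randomisation and can show a difference when none exists. The mechanism follows from the document alone. The sizes do not: about 0.4 to 1.3 points among achievers and 1.0 to 2.9 among non-achievers rest on the assumed proportions, a correlation of 0.1 to 0.3 and no baseline adjustment, and the direction is unknown. The primary analysis, the sample size of 350 and the error rate of the main test are unaffected. It is worth correcting because the result could not be interpreted whichever way it fell, but it does not threaten the trial's main conclusion.

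**What to change.** Delete the target-achievement item from the list under Subgroup analysis. Keep achievement as the per-group descriptive report, with reasons, already promised under General analytic principles.

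Optionally, if variation in effect by rate is of interest, use baseline resting heart rate as the subgroup factor. It is measured by ECG before randomisation, is listed in Table 1 and has the same meaning in both arms. It answers a different question and says nothing about the effect of reaching a target. If the effect among those able to reach target is itself wanted, it needs a principal-stratum or complier-average estimator with its assumptions stated.

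The cost is a change of wording, with no new data. The loss is an exploratory comparison that clinicians would find attractive but that could not be interpreted.

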#### Statistical analyses

The statistical analyses will be performed using STATA 17 [8].

##### Analysis of continuous data

Continuous outcomes will be presented as means and SD with 95% confidence intervals (Cis). We will analyze continuous outcomes using linear regression adjusting for “site,” type of atrial fibrillation (persistent/ permanent), LVEF (≥ 40% or < 40%), and the baseline value of the score (all as fixed effects) [22].

In the quality-of-life analysis, our primary analyses will only be of participants who are alive and able to fill out the questionnaires at the 12-month follow-up will be included. If a participant has died, he/she will not be included in this analysis. To assess the potential influence of participants who die, we will present a sensitivity analysis as a supplement where participants who die will have a value of 0 imputed for quality of life (these data will be analyzed as count data, see paragraph below).

An example of continuous data is collected from the following outcome: “SF-36 questionnaire score (physical component).”

##### Analysis of dichotomous data

Dichotomous outcomes will be presented as proportions of participants in each group with the event, as well as relative risks with 95% CIs. Dichotomous outcomes will be analyzed using logistic regression adjusting for “site,” type of atrial fibrillation at inclusion (persistent/permanent), and LVEF (≥ 40% or < 40%) (all as fixed effects). Odds ratios will be transformed to relative risks using the NLCOM command in STATA [8].

An example of a dichotomous data is collected from the following outcome: “Switch to rhythm control therapy.”

##### Analysis of count data

Count data will be presented as medians and interquartile ranges. We will analyze count data using van Elteren’s test stratifying for “site” and report Hodges Lehman median differences and confidence intervals [12, 23, 24].

An example of a count outcome is collected from the following outcome: “Number of hospital admissions.”

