### Randomization

This trial uses centralized randomization at Open Patient data Explorative Network (OPEN), where varying block sizes unknown to the investigators will be used. Randomization is stratified for (1) site of inclusion, (2) persistent/permanent atrial fibrillation (6 months before inclusion), and (3) left ventricular ejection fraction (LVEF) (≥ 40% or < 40%). Participants are be randomly allocated to the lenient versus the strict rate control strategy arm in an 1:1 ratio [3].

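### The deaths-as-zero sensitivity analysis of quality of life changes the covariates and the scale as well as the handling of deaths, because it is sent to a rank test stratified by site only

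*SAP article*

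**What the plan says.** Under Randomization there are three stratification factors: "Randomization is stratified for (1) site of inclusion, (2) persistent/permanent atrial fibrillation (6 months before inclusion), and (3) left ventricular ejection fraction (LVEF", the last dichotomised at 40%. General analytic principles sets the adjustment rule: "We will adjust all regression analyses for the stratification variables we used for the randomization process", and adds the baseline value for continuous outcomes. Analysis of continuous data follows this rule. The primary linear model for the SF-36 physical component score carries site, AF type, LVEF and the baseline score, and it is restricted to participants who are alive and able to complete the questionnaire at 12 months.

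The same section plans a supplementary analysis to gauge the influence of deaths: "participants who die will have a value of 0 imputed for quality of life (these data will be analyzed as count data, see paragraph below". The section it points to, Analysis of count data, says: "We will analyze count data using van Elteren’s test stratifying for “site” and report Hodges Lehman median differences". No section adds AF type, LVEF or a baseline value to that test. The other outcomes labelled as counts are hospital-free days (secondary) and number of hospital admissions (exploratory).

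**The concern.** A sensitivity analysis is informative when it changes one thing. This one is meant to show whether leaving out the dead affects the quality-of-life result. As written, four things change together: the dead enter with a score of 0, the baseline score leaves the model, two of the three randomisation factors leave it, and an adjusted mean difference becomes a rank test with a Hodges-Lehmann difference. No intermediate analysis is planned that would separate them. If the primary result is significant and this one is not, the reader cannot tell whether the deaths or the lost precision are responsible. The trial's conclusions rest on this outcome, and the primary model leaves the dead out, so the check should be readable.

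For hospital-free days and admissions the issue is narrower. Allocation is balanced within AF type and LVEF, and a test that ignores those factors does not use that balance. It then tends to be slightly conservative.

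**Working it through.** **1. The plan's own figures.** Inputs from Sample size: 3 points, SD 10, power 80%, type I error 5%, taken as two-sided.

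n per arm = 2(1.960 + 0.842)² × 10² / 3² = 174.4, rounded up to 175, so 350 in total. This reproduces. For hospital-free days (3 days, SD 9, 15% allowance) power is 82.8% with 350/1.15 participants and 82.0% with 350 × 0.85, against 82.1% stated. Neither figure depends on how the test is stratified.

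**2. Cost of the dropped covariates in the deaths-as-zero analysis.** This was simulated with 350 participants, five equal sites (Table 1 lists five), permuted blocks within the 5 × 2 × 2 = 20 cells, and 2,000 runs per scenario. Assumptions not in the document:
- a 3-point effect in survivors and SD 10 within strata
- 5% deaths, equal in both arms
- half with permanent AF and 20% with LVEF < 40%
- effects of 2 points (AF type) and 4 points (LVEF)

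The Monte Carlo standard error is √(0.68 × 0.32/2000), about 1.0 point.

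| Baseline correlation | Van Elteren, site only | Van Elteren, 20 cells | Rank ANCOVA, strata and baseline | Gain over site only |
|---|---|---|---|---|
| 0.3 | 67.4% | 67.6% | 72.4% | 5.0 |
| 0.5 | 68.3% | 67.4% | 78.0% | 9.7 |
| 0.7 | 67.3% | 67.3% | 86.7% | 19.4 |

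At correlation 0.5 the comparison (site only against rank ANCOVA) is 72% against 82% with 2% deaths, and 58% against 66% with 10% deaths. Almost all of the gain comes from the baseline score; restoring the strata alone does little.

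**3. Why attribution fails.** Approximate power of the primary model in survivors, with 350 × 0.95 / 2 = 166.25 per arm: Φ(3 / [10√(1 − r²) × √(2/166.25)] − 1.96).
- r = 0.3: Φ(2.867 − 1.960) = 81.8%
- r = 0.5: Φ(3.158 − 1.960) = 88.5%
- r = 0.7: Φ(3.830 − 1.960) = 96.9%

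The fall from the primary model to the planned sensitivity analysis then splits as follows.

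| r | Total fall | Deaths and rank scale | Dropped covariates | Share from covariates |
|---|---|---|---|---|
| 0.3 | 81.8 − 67.4 = 14.4 | 81.8 − 72.4 = 9.4 | 5.0 | 35% |
| 0.5 | 88.5 − 68.3 = 20.2 | 88.5 − 78.0 = 10.5 | 9.7 | 48% |
| 0.7 | 96.9 − 67.3 = 29.6 | 96.9 − 86.7 = 10.2 | 19.4 | 66% |

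This sets a normal-theory figure beside simulated ones and is approximate. Under these assumptions, between a third and two thirds of the lost power has nothing to do with the deaths.

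**4. Omitting AF type and LVEF alone.** In the same simulation, type I error with site only is 4.9%, and 4.2% when the strata effects are doubled to 4 and 8 points (Monte Carlo standard error about 0.5 points). With doubled effects, power is 64.4% for site only and 67.1% for 20 cells, a gain of 2.7 points. With no strata effects, 20 cells gives 67.1% against 69.4%, slightly worse. A separate simulation of 3,000 runs per scenario gives 4.5% against 5.1% error and no power gain if the two factors explain 6% of the variance. At 14% explained it gives 3.5% against 5.0% error and 78.5% against 81.9% power. For hospital-free days, with 15% against 45% hospitalised by LVEF group (assumed), the error is 3.9% against 5.0%. Power for hospital-free days was not simulated.

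**The case against.** Several stronger readings are tempting, and the document does not support them.

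- *The plan contradicts itself.* The adjustment rule is limited to regression analyses, and van Elteren's test is not one. The stratum is prespecified without ambiguity. This is a mismatch with the design, not a contradiction.
- *The test is invalid or badly underpowered for count outcomes.* Every simulated error rate for the site-only test is below 5%. The larger deficits need strong strata effects, for which the document gives no figures. Baseline adjustment does not arise for hospital-free days or admissions, which have no baseline score.
- *The trial's conclusion is at risk.* The primary model already carries all three factors and the baseline score. The count outcomes are declared hypothesis-generating, and the deaths-as-zero analysis is a supplement.
- *The wrong AF variable will be used.* Randomization describes "persistent/permanent atrial fibrillation (6 months before inclusion", while the dichotomous model uses "type of atrial fibrillation at inclusion (persistent/permanent". A reader might infer two different variables, but the general rule ties the covariates to the variables used in randomisation, which largely settles it.

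It is also fair to say that a cluster of zeros makes a rank method reasonable, and that rank ANCOVA by itself still differs from the primary model in scale. That stands, and it is why a survivors-only rank analysis is needed alongside. Attribution under the present plan is weakened, not impossible. What remains is that choosing a rank method does not require giving up the covariates.

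**Conclusion.** The point holds for the deaths-as-zero analysis. It gives up about 5 to 19 points of power over assumed baseline correlations of 0.3 to 0.7 with 5% deaths, and it confounds the handling of deaths with the change in covariates and scale. The correlation, death rate and strata effects are assumptions; at correlation 0.5 the loss also appears at 2% and 10% deaths. For hospital-free days and admissions the matter is minor: a valid, at most mildly conservative test, with about 0 to 3 points of power to gain, and nothing to gain if the factors are not prognostic. It is worth correcting because the change is one of wording and the factors and baseline score are already part of the plan.

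**What to change.** 1. Deaths-as-zero analysis: rank participants who die below all survivors and use a rank ANCOVA adjusted for baseline score, site, AF type and LVEF. Run the same rank ANCOVA in survivors alone. These two analyses then differ only in the handling of deaths, and the survivors-only one also links back to the primary linear model.
2. Hospital-free days and admissions: stratify van Elteren's test by site, AF type and LVEF, using the values recorded in the randomisation system. State the pooling rule for sparse cells in advance, for example pooling small sites within AF type by LVEF.

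The cost is SAP wording and one additional supplementary analysis. The downside is that some cells will carry little information. If 20% have LVEF < 40% (assumed), 350 × 0.20 = 70 participants fall in 10 cells, about 7 each; at 10% it is 35, or 3.5 each. The pooling rule must therefore be fixed before the data are seen. No change to the primary analysis or the sample size is needed.

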#### Secondary outcomes

Hospital-free days (HFDs), analyzed as count data. We define HFDs as all days alive that are spent outside an acute-care hospital, long-term acute-care hospital (LTACH), or in an emergency department (ED), including days spent wholly or in part under “observation” status. All other days, including days spent in a long- or short-stay nursing facility, inpatient hospice facility, or rehabilitation facility count as hospital-free, as would all days at home, including those with home-based medical services [7]Symptoms due to atrial fibrillation assessed using the Atrial Fibrillation Effect on Quality-of-Life questionnaireQuality of life using the SF-36 questionnaire (mental component score)Serious adverse events, defined according to The International Conference on Harmonization as any untoward medical occurrence that resulted in death, was life-threatening, required hospitalization or prolongation of existing hospitalization, and resulted in persistent or significant disability or jeopardized the patient [4]

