#### Hospital-free days

Using a minimal important difference of 3 days, a SD of 9 days, a risk of type I error of 5%, and accounting for the fact that the data is expected not to be normally distributed (adding 15% to the required sample size) [11], we will be able to reject the null hypothesis that the population means of the experimental and control groups are equal with probability (power) of 82.1% [12].

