#### Serious adverse events

Using a proportion of participants with one or more serious adverse events in the control group of 20%, a relative risk reduction of 30%, and a risk of type I error of 5%, we will be able to reject the null hypothesis with probability (power) of 32%.

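### The 3-day criterion for hospital-free days is a difference in means, but the only planned estimate is a Hodges-Lehmann difference, which is exactly 0 (0 to 0) if fewer than about 44% of each arm lose any day

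*SAP article*

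**What the plan says.** The Secondary outcomes section lists first "Hospital-free days (HFDs), analyzed as count data". Days count only if the participant is alive and outside acute-care hospitals and emergency departments; observation stays also count against the total. Number of hospital admissions is an exploratory outcome, likewise handled as count data.

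The section on count data fixes the presentation ("Count data will be presented as medians and interquartile ranges") and the analysis: van Elteren's test, stratified by site, after which the authors will "report Hodges Lehman median differences and confidence intervals". It names no other effect measure.

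The power section for hospital-free days begins "Using a minimal important difference of 3 days, a SD of 9 days". After a 15% allowance for non-normality, it gives 82.1% power to reject equality of the two population means. General analytic principles then states that "assessments of clinical significance will be based on the anticipated intervention effects defined in the sample size and power estimations".

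Two other sections bear on the point. The power section for serious adverse events assumes that 20% of controls have at least one, with a 30% relative reduction, and the definition of such an event includes death and hospitalisation. Under Subgroup analysis, "The subgroup analyses will be performed for primary and secondary outcomes", using a test of interaction between treatment and subgroup indicator.

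**The concern.** The benchmark and the estimate are on different scales. A Hodges-Lehmann difference is the median of all between-arm pairwise differences. It equals the mean difference when one arm's distribution is the other's shifted by a constant. Hospital-free days have a ceiling: a participant who is alive and never in hospital scores the full follow-up period. If most participants in both arms sit there, most pairs are tied and their median difference is 0.

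The reported effect could then be 0 days with a zero-width interval although the mean difference is the 3 days the plan calls important, possibly next to a significant van Elteren p-value. A reader would take this as a precisely estimated absence of effect. The clinical-significance step for this outcome would have nothing usable to compare with 3 days. In addition, van Elteren's test has no interaction term, so the subgroup test required for this secondary outcome has no model to run in.

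**Working it through.** **Inputs.** 350 participants, 1:1, so 175 per arm; 12-month primary time point; target 3 days, SD 9; 20% of controls with a serious adverse event, hence 0.7 × 20% = 14% in the other arm. The share with any lost day (in hospital, in an emergency department, under observation, or dead) is not stated. Taking 20% and 14% for it is an assumption, so a range is shown.

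**The plan's own figure.** Power ≈ Φ(3 / (9 × √(4/N)) − 1.96).
- N = 350/1.15 = 304: 82.8%.
- N = 350 × 0.85 = 297.5: 82.0%.
- N = 350 without allowance: 87.7%.

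The stated 82.1% is reproduced, as the power of a comparison of means.

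**When the estimate collapses.** There are 175 × 175 = 30,625 pairwise differences. The rank-based 95% interval cuts them at

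30,625/2 ± 1.96 × √(30,625 × 351/12) = 15,312.5 ± 1.96 × 946.5 = 15,312.5 ± 1,855,

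that is, at 43.9% and 56.1% of the ordered differences. A difference in favour of one arm needs a lost day in the other arm's member of the pair. The proportion of differences in either direction therefore cannot exceed the share with any lost day in the arm that is worse off in those pairs. If that share is below 43.9% in each arm (at most 76 of 175), the estimate and both limits are 0, whatever the lengths of stay. At 20% and 14%, at least 0.80 × 0.86 = 69% of pairs are tied.

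Pairing within site changes little. With the five sites of Table 1 taken as equal (35 v 35 each, an assumption), there are 5 × 1,225 = 6,125 pairs, and the half-width is 1.96 × √(5 × 1,225 × 71/12) = 373, or 6.1% of them. The cut is again at 43.9%.

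**Simulation.** 175 per arm, unstratified, 300 to 400 trials per scenario, no deaths, true mean difference 3 days. The share with any lost day is 30% lower in the better arm.

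| Control share with any lost day | Estimate and interval 0 (0 to 0) | Estimate 0 |
|---|---|---|
| 20% | 100% | 100% |
| 30% | 100% | 100% |
| 40% | 99–100% | 100% |
| 50% | 62–76% | 98–99% |
| 60% | 3–13% | 45–73% |
| 70% | 0% | 3–12% |

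Above 70% the estimate was typically 2 days. With equal shares in both arms and the effect only in length of stay, the result was 0 (0 to 0) in 100% of trials at 20–30%, 99.8% at 40%, 83% at 50% and 25% at 60%. A pure 3-day shift without a ceiling gave 2.97 days.

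In the 20% v 14% runs (pooled SD 6.7 to 10.4), a rank test was significant in 41–52% of trials, although the estimate and interval were 0 (0 to 0) in all of them. A t-test rejected in 80–100%.

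**Admissions.** With negative binomial counts and a rate ratio of about 0.65 to 0.70, the result was 0 (0 to 0) in 99–100% of trials when at least half of controls had no admission, and in 73% when 40% had none.

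**The case against.** A reader might infer that the reported difference will certainly be 0 (0 to 0) and that the 3-day criterion can never be met. The document does not support this. The share with any lost day is borrowed from a power input for another outcome. Emergency-department or observation contacts that are not serious adverse events, and deaths, could lift it above 20%. From about 60% the collapse is no longer the usual result.

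The plan's figures also fit together poorly. With equal stays in both arms, 20% v 14% hospitalised gives 3 days only if 0.06 × L = 3, so L = 50 days per hospitalised participant. The control SD is then at least 50 × √(0.2 × 0.8) = 20, not 9. An SD near 9 requires very unequal stays: if the other arm averages 5 days, controls must average (3 + 0.14 × 5)/0.20 = 18.5. This stands as a caution about the 20% v 14% simulations. The 43.9% bound does not depend on length of stay.

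The plan treats secondary and exploratory results as hypothesis-generating, van Elteren's test is valid, and readers would also see its p-value and interquartile ranges. All of that stands and limits the severity.

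A mean difference has its own weakness. The outcome counts days alive, so deaths enter heavily. Assuming deaths spread evenly over 365 days and added to SD 9, the variance is 81 + q × 365²/3 − (q × 182.5)². For mortality q of 1%, 2% and 5%, the SD is about 23, 31 and 47, and power for 3 days about 23%, 15% and 9%. That argues for adding a mean difference beside the rank analysis rather than discarding the latter. It does not make a Hodges-Lehmann difference comparable with a mean-based criterion.

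The missing interaction term is a separate matter from ties. It concerns hospital-free days only, since admissions are exploratory.

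**Conclusion.** The scale mismatch is in the text and holds without assumptions: the 3 days are a difference in means, and the only planned estimate is a median of pairwise differences. How much it matters depends on one unstated quantity. Below about 44% of each arm with any lost day, the result is 0 (0 to 0) by arithmetic. Near 50% of controls it remains likely (62–83% of simulated trials), and from about 60% it fades. The plan's 20% serious-adverse-event figure points to the first case but does not establish it.

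Number of admissions shares the problem when most participants have none, but has no 3-day criterion to miss. The defect lies in the effect summary, not in the test, and the primary conclusion on the SF-36 physical component score is unaffected. It should be fixed before the data are analysed, because otherwise the clinical-significance step for the first-listed secondary outcome may be unusable.

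**What to change.** - Keep van Elteren's test for the p-value; the Hodges-Lehmann difference may stay beside it.
- For hospital-free days at 12 months, add the arm means and a mean difference adjusted for the stratification variables, with a robust or bootstrap 95% interval. State that the 3 days are judged against this difference.
- Run the subgroup interaction tests for hospital-free days in this mean model.
- For number of admissions, add a rate ratio from a negative binomial or robust Poisson model.
- Report deaths by arm beside hospital-free days.

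The cost is a few sentences in the plan and a few lines of code. The price is precision. The approximate 95% half-width for the mean difference is 1.96 × SD × √(2/175): 1.9 days at SD 9, but about 4.8 days at SD 23 (1% mortality) and 6.5 days at SD 31 (2%). The interval may therefore be too wide to settle the 3-day question, but it would show that uncertainty, which an interval of 0 to 0 would hide.
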